## Methods

### Study design

A longitudinal prospective cohort study will be conducted to identify clinical phenotypes and prognostic factors for outcomes in pain and disability in individuals with hip OA undergoing THA (HIPPROCLIPS, ClinicalTrials.gov Identifier: NCT05265858). Ethical approval was obtained from the medical ethical committee of Hospital East-Limburg and Hasselt University (B3712021000002). Measurements will be performed at five major timepoints: one week before THA (T0), during the first week after THA (T1), and six weeks (T2), three months (T3), 12 months after THA (T4). During the first week after THA, participants will be asked to complete a minor set of questionnaires on the first, the third, the fifth, and the seventh postoperative day. A timeline and schematic overview of the HIPPROCLIPS-trial can be found in Fig. 1. The HIPPROCLIPS-trial is divided in four sub-studies based on cross-sectional and longitudinal analyses, details on the different studies can be found in Table 1.

**Table 1 Tab1:** Overview of the HIPPROCLIPS-trial studies

Study	Objective	Research Questions (RQ)	Phenotyping variables or candidate prognostic factors	Outcome variables	Design and main statistical method
1	To determine the influence of traumatic experiences and mental disorders on the pain processing of individuals with hip OA and shortly after THA	1. To which extent are traumatic experiences and mental disorders associated with preoperative pain processing in individuals with hip OA waiting for THA? 2. To which extent are traumatic experiences and mental disorders associated with pre- and early postoperative pain-related cognitions and emotions in individuals with hip OA undergoing THA?	- Traumatic experiences (T0) - Mental disorders (T0)	Primary: QST (T0) Secondary: Pain-related cognitions and emotions, other pain-related variables (T0, T1)	**Design**: cross-sectional (RQ1) and longitudinal analysis (RQ2) **Main statistical method**: LASSO regression

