2	To identify preoperative clinical phenotypes in individuals with hip OA and their prognosis for outcomes in pain and disability after THA	1. Which clinical phenotypes exist in individuals with hip OA waiting for THA, based on a set of biopsychosocial characteristics? 2. What is the prognostic value of these clinical phenotypes for outcomes in pain and disability after THA?	- Sociodemographic and biomedical information (T0) - Pain-related cognitions and emotions (T0) - Traumatic experiences (T0) - Mental disorders (T0) - Self-efficacy (T0) - Social support (T0) - Perceived stress (T0) - QST (T0) - Other pain-related variables (T0)	Primary: HOOS Secondary: NPRS, PBM, SF-36, PSFS, GPE, Satisfaction, Muscle Strength	**Design**: Cross-sectional analysis of baseline data **Main statistical method**: Decision Tree learning
3	To identify pre- and early postoperative prognostic factors for long-term outcomes in pain and disability after THA in individuals with hip OA	1. To which extent do pre-operative traumatic experiences, mental disorders, pain-related cognitions and emotions, self-efficacy, social support, and central pain mechanisms predict long-term postoperative pain and disability after THA for hip OA? 2. To which extent do early postoperative pain-related cognitions and emotions predict long-term pain and disability after THA for hip OA?	- Pain-related cognitions and emotions (T0) - Traumatic experiences (T0) - Mental disorders (T0) - Self-efficacy (T0) - Social support (T0) - QST (T0)	Primary: HOOS Secondary: NPRS, PBM, SF-36, PSFS, GPE, Satisfaction, Muscle Strength	**Design**: longitudinal prospective **Main statistical method**: Gradient Boosting Algorithms

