4	To identify postoperative clinical phenotypes based on biopsychosocial characteristics at different timepoints up to one year after THA for hip OA	1. Which postoperative clinical phenotypes exist based on biopsychosocial characteristics at different timepoints up to one year after THA for hip OA? 2. What is the relationship between preoperative and postoperative clinical phenotypes in individuals with hip OA and after THA? 3. To which extent do pre- and early postoperative factors predict the belonging to a clinical phenotype after THA?	- Sociodemographic and biomedical information (T2, T3, T4) - Pain-related cognitions and emotions (T2, T3, T4) - Traumatic experiences (T2, T3, T4) - Mental disorders (T2, T3, T4) - Self-efficacy (T2, T3, T4) - Social support (T2, T3, T4) - Perceived stress (T2, T3, T4) - QST (T2, T3, T4) - Other pain-related variables (T2, T3, T4)	Primary: HOOS Secondary: NPRS, PBM, SF-36, PSFS, GPE, Satisfaction, Muscle Strength	**Design**: longitudinal prospective **Main statistical method**: Recurrent Neural Networks

*Legend: OA = osteoarthritis, THA = total hip arthroplasty, QST = Quantitative Sensory Testing, NPRS = Numeric Pain Rating Scale, HOOS = Hip Disability and Osteoarthritis Outcome Score, PBM = Performance-Based Measures, SF-36 = 36-item Short-Form Health Survey, PSFS = Patient Specific Functioning Scale, GPE = Global Perceived Effect. Timepoints: one week before THA (T0), during the first week after THA (T1), and six weeks (T2), three months (T3), 12 months after THA (T4)*

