Quantitative Sensory Testing (QST)	Cold detection threshold (CDT) (local, remote)	T0, T2, T3, T4
	Warmth detection threshold (WDT) (local, remote)	T0, T2, T3, T4
	Cold Pain Threshold (CPT) (local, remote)	T0, T2, T3, T4
	Heat Pain Threshold (HPT) (local, remote)	T0, T2, T3, T4
	VAS 60 Temperature	T0, T2, T3, T4
	Temporal Summation of Pain (TSP)	T0, T2, T3, T4
	Conditioned Pain Modulation (CPM)	T0, T2, T3, T4
**Outcome variables**	**Variables**	**Timepoints**
Self-reported pain and disability	Hip disability and Osteoarthritis Outcome Score (HOOS) [62]	T0, T2, T3, T4
	Patient Specific Functioning Scale (PSFS) [63]	T0, T2, T3, T4
	Numerical Pain Rating Scale (NPRS) [64]	T0, T1, T2, T3, T4
Health-related quality of life	36-item Short-Form Health Survey (SF-36) [65]	T0, T2, T3, T4
Effect of THA on hip complaints in general	Global Perceived Effect (GPE) [66]	T0, T1, T2, T3, T4
Satisfaction with the outcome after THA	Satisfaction (NRS)	T0, T1, T2, T3, T4
Performance-based measures (PBM) [67]	30 s chair stand test (30s-CST)	T0, T2, T3, T4
	40 m fast paced walk test (40 m FPWT)	T0, T2, T3, T4
	10-step stair climb test (10-step SCT)	T0, T2, T3, T4
Muscle strength testing [68]	Isometric muscle strength of the hip flexors, extensors, abductors, adductors, external rotators	T0, T2, T3, T4

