If this approach is not successful, random decision forest will be used [94]. However, it is preferred to keep the model as simple as possible to ease the clinical interpretation.

For the study 3 gradient boosting algorithms will be applied to the dataset to select the best prognostic factors for long-term outcomes in terms of pain and disability [95]. Gradient boosting techniques are a type of ensemble learning that combines numerous weak predictors to create a more accurate one. It adds decision trees to the model in an iterative manner, with each new tree aiming to correct the errors of the preceding trees. Gradient boosting algorithms are especially effective when working with complex data and are frequently capable of achieving high accuracy on a wide variety of problems compared to stepwise linear regression. Previous contralateral THA will be included as a covariate in the analysis to account for possible bias due to knowledge of surgical procedures and postoperative recovery course.

Finally, for study 4, recurrent neural networks (RNN) will be applied to identify postoperative clinical phenotypes based on the multiple data points (repeated measurements during T2, T3, and T4) [96]. RNNs are a sort of neural network architecture that can process sequences of inputs, such as time series. They can keep an internal memory of previous inputs and use it to make predictions about future inputs. RNNs are particularly good for modelling complex temporal interactions. When working with sequential data, RNNs tend to be more flexible and robust than stepwise regression. They are able of modelling complex temporal relationships and less susceptible to overfitting.

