
In addition to the strengths and innovative aspects of this study, there are also some practical issues and potential limitations to consider. In a recent systematic review [101], we investigated contextual prognostic factors for outcomes in the International Classification of Functioning, Disability and Health activity and participation domain after THA in individuals with hip OA. In this review, the main issues in prognostic factor research in individuals after THA for hip OA were discussed. Currently, most studies on prognostic factors for outcomes after THA have a high risk of bias, with mainly problems regarding study attrition and confounding. Therefore, an important practical consideration for this study will be to limit drop-out and accommodate study attrition of participants. The timepoints for follow-up measurements will therefore be scheduled together with the postoperative monitoring appointments with the surgeon to reduce the burden on participants. Furthermore, confounders will be clearly defined and measured using valid and reliable tools, and will be appropriately accounted for in the statistical analysis. One of the limitations of this study will be that generalizability will be limited to individuals with hip OA eligible for THA, and individuals undergoing direct anterior approach THA, since there is a significant preselection of individuals with hip OA undergoing direct anterior approach THA. Furthermore, no external validation is included in this study protocol. When a certain subgroup classification or prognostic factors will be identified, replication of the findings will be necessary in another sample.

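### Study 3 names one covariate and lists no baseline severity, age, sex, BMI or comorbidity, so as written it cannot show what the psychological factors add beyond preoperative status

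*Protocol article*

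**What the plan says.** Four places in the protocol article bear on this.

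- **Table 1, Study 3 row.** The candidate factors are "Pain-related cognitions and emotions (T0) - Traumatic experiences (T0) - Mental disorders (T0) - Self-efficacy (T0) - Social support (T0) - QST (T0"). The outcomes are HOOS (primary) and several secondary measures, with no timepoint attached.
- **Statistical analysis, Study 3.** Gradient boosting is to select the best prognostic factors. The one covariate named is in this sentence: "Previous contralateral THA will be included as a covariate in the analysis to account for possible bias".
- **Table 1, Studies 2 and 4.** Both rows open with a block that Study 3 lacks: "Sociodemographic and biomedical information (T0") for Study 2 and "Sociodemographic and biomedical information (T2, T3, T4") for Study 4.
- **Discussion, limitations.** After naming confounding as a main problem of this literature, the article says "confounders will be clearly defined and measured using valid and reliable tools, and will be appropriately accounted for in the statistical analysis". It names no confounder there.

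Table 2 shows that the variables exist. Age, sex and height are taken at T0, and body weight and comorbidity count at T0 and each later visit. The text derives BMI from height and weight. "Hip disability and Osteoarthritis Outcome Score (HOOS) [62]" is measured at T0, T2, T3 and T4, but Table 2 lists it only as an outcome, and no row of Table 1 lists its T0 value as a predictor.

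**The concern.** The article itself supplies the reasons to adjust. The Background calls comorbidities an already identified prognostic factor for pain and disability after THA. It also says that anxiety symptoms go with more pain and disability both before and after surgery. If worse preoperative status predicts worse postoperative status, anything that tracks preoperative status will look prognostic, whether or not it carries information of its own.

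Gradient boosting does not protect against this. When T0 HOOS is not among the inputs, the algorithm uses whatever listed variable best stands in for it. Fear-avoidance, perceived injustice and HADS scores are natural candidates.

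The Discussion expects the identified factors to improve the accuracy of existing prognostic models, to help identify patients at risk and to inform enrichment trials. For those uses the question is whether a factor predicts beyond what is already known from the preoperative score and basic patient data. A model on the listed factors alone cannot answer it.

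**Working it through.** **1. Is the omission visible in the text?** Table 2 puts the sociodemographic and biomedical block under the same heading as the psychological factors, and that heading is the one over the Table 1 column. Studies 2 and 4 include the block there and Study 3 does not. The Study 3 analysis text adds only contralateral THA. T0 HOOS, age, sex, BMI and comorbidity count are therefore in neither the list nor the named adjustment.

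**2. Do the 12 predictors of the sample size suggest hidden room?** The factors listed for Study 3 fill 17 rows of Table 2: 3 cognitions and emotions, 2 trauma, 3 mental disorders, 1 self-efficacy, 1 social support and 7 QST. Counting the two HADS subscales and the local and remote sites of four QST measures separately gives 17 + 1 + 4 = 22. Twelve leaves no evident space for baseline covariates.

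**3. How large could the proxy effect be?** The documents give no correlations, so these are assumed. Let b be the correlation of preoperative severity with the outcome and ρ that of a factor with severity, each 0.3 to 0.5. The factor has no effect of its own. Its correlation with the outcome is then r = ρ × b. With n = 200 × (1 − 0.20) = 160, two-sided power at 5% is approximately Φ(atanh(r) × √(n − 3) − 1.96), plus a negligible lower tail.

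| ρ | b | r | atanh(r) × √157 | Share significant |
|---|---|---|---|---|
| 0.3 | 0.3 | 0.09 | 1.13 | 20% |
| 0.3 | 0.5 | 0.15 | 1.89 | 47% |
| 0.5 | 0.5 | 0.25 | 3.20 | 89% |

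With severity adjusted for linearly and measured without error, the share is 5%. This is a single-factor linear illustration, not a calculation for the planned boosting model.

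**4. What if several such factors are entered together?** Take five factors that are independent given severity (assumed). Each null factor then has standardised coefficient ρb/(1 + 4ρ²): 0.09/1.36 = 0.066 at the low end and 0.25/2 = 0.125 at the high end. The model R² is 5 × 0.09 × 0.066 = 0.030 and 5 × 0.25 × 0.125 = 0.156. The variance inflation is (1 + 3ρ²)/((1 − ρ²)(1 + 4ρ²)), that is 1.026 and 1.167. The noncentrality is

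- low: 0.066 × √160 / √(0.970 × 1.026) = 0.84, significant in about 13% of samples;
- high: 0.125 × √160 / √(0.844 × 1.167) = 1.59, significant in about 35%.

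The problem shrinks but stays well above 5%.

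**5. Can 200 patients carry the extra terms?** The article gives 12 variables, 80% power, effect size 0.15 and 20% dropout. It gives neither the effect-size metric nor alpha, so f² = 0.15 and alpha = 0.05 are assumptions. I use the noncentral F test of R² with λ = f² × N.

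- The article's own figure: N = 127 gives λ = 19.05 on (12, 114) df and power 80.2%, while N = 126 gives 79.8%. Enrolment is 127/0.8 = 159, not 200. The mismatch is a separate matter; here it only means there is slack.
- 12 predictors, 160 analysed: λ = 24, (12, 147) df, power 90.9%.
- 17 predictors tested together (12 plus the five): λ = 24, (17, 142) df, power 85.0%. Counting contralateral THA as an eighteenth gives 83.8%.
- The 12-factor block tested over five covariates: (12, 142) df, power 90.8% with λ = 0.15 × 160 = 24, or 89.7% with λ = 0.15 × (12 + 142 + 1) = 23.25.

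**The case against.** The strongest reply is that the Table 1 row is not a full list of model inputs. It omits contralateral THA, which the analysis text puts in the model. It also shows only T0 factors, although the second research question in that row needs early postoperative ones. The text does not call contralateral THA the only covariate, and the Discussion commits to accounting for confounders. The full plan may name them. A change-from-baseline outcome is not ruled out either, since Table 1 gives HOOS no timepoint for this study.

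This stands as far as it goes. A reader might infer that Study 3 will definitely be run without baseline severity and demographics, or that the article contradicts its own promise on confounding. The documents support neither: the set is unnamed, not excluded. What remains is that the places which specify Study 3 do not carry the promise out, while the parallel rows for Studies 2 and 4 do list the missing block.

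Three further objections limit the claim.

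- The research question asks to what extent the factors predict, and a factor that predicts through severity is still prognostic. That is right, but the Discussion's intended uses depend on added value.
- A reader might take 20% to 89% as a false-positive rate for the planned analysis. It is not: the correlations are assumed, the calculation takes one factor at a time, and the article states no 5% test for the boosting model.
- Forcing covariates into a tree ensemble is not just a matter of listing them. This is correct, and the fix allows for it.

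**Conclusion.** The point holds in a limited form. As printed, Study 3's factor list and its one named covariate leave out T0 HOOS, age, sex, BMI and comorbidity count, all of which are collected, and the general promise in the Discussion is not carried into the analysis text. If the model is run that way, it could pick psychological factors because they track preoperative severity, and it could not show whether they add to it.

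The size depends on correlations the documents do not give. Under assumed values of 0.3 to 0.5 a factor with no effect of its own is flagged in about 20% to 89% of samples one at a time, and in about 13% to 35% with five such factors jointly. Both are linear illustrations.

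Study 1 shows a similar pattern, with "Traumatic experiences (T0) - Mental disorders (T0") as its only listed predictors of pain processing. Study 2 compares the prognosis of phenotypes without listing T0 HOOS. Both are secondary; no size was worked out for them.

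**What to change.** In the Study 3 paragraph of Statistical analysis and in the Study 3 row of Table 1:

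- Name T0 HOOS, age, sex, BMI and number of comorbidities, beside previous contralateral THA, as the base for the HOOS model. For each secondary outcome use its own T0 value where one is meaningful; for perceived effect of surgery and satisfaction with its outcome it may not be.
- Because tree boosting chooses its own splits, enter these variables as a base model or offset, not as extra candidates.
- Report the predictive gain of the candidate factors beyond that base.
- Restate the count of 12 independent variables in the sample-size sentence to match.

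As secondary changes, consider age and sex in the Study 1 models and T0 HOOS in the Study 2 comparison of phenotype prognosis.

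**Cost.** No new data are needed. The model gains a few terms, and the modelling step changes slightly to hold the base fixed. On the assumptions above, power with 160 analysed stays at about 85% for 17 predictors together and about 90% for the 12-factor block. The psychological factors will probably show smaller apparent effects.

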## Discussion

The present study will contribute to the knowledge needed to improve pain and disability in individuals with hip OA and after THA. From a clinical point of view, the identification of clinical phenotypes before and after THA, based on a set of biopsychosocial characteristics, may represent a fundamental step towards the development of pre- and postoperative precision medicine pathways for individuals with hip OA undergoing THA. From a scientific perspective it can provide a basis for subgroup analyses in clinical trials, or it can facilitate the implementation of enrichment strategies in randomized controlled trials. Furthermore, prognostic factors for outcomes in pain and disability after THA will contribute to the improvement of outcomes in pain and disability by enabling healthcare providers to identify persons at risk of poor outcome, and consequently increasing options for shared decision making, expectation management and precision medicine [18].

This longitudinal prospective cohort study has several strengths and innovative aspects. First and foremost, phenotyping variables across all domains of the biopsychosocial framework are included, which has been a missing element in studies investigating clinical phenotypes in individuals with hip OA [15, 97]. Moreover, except for the sociodemographic and biomedical variables, all phenotyping variables are modifiable and treatable and thus of great clinical importance. An important innovative aspect is that this will be the first study in individuals with hip OA to include both self-reported biopsychosocial characteristics and mechanistic pain profiling using QST. This allows us to investigate whether clinical phenotypes are characterized by different pain mechanisms, and consequently may need different treatment approaches. Additionally, the primary outcome measures are situated within the clinically relevant activity and participation domain of the International Classification of Functioning, Disability and Health, and include both self-reported and performance-based outcome measures. Moreover, the inclusion of secondary outcome measures such as quality of life, outcome satisfaction, global perceived effect, and muscle strength, in addition to outcome measures related to pain and disability, also contributes to the clinical significance of this study. This allows assessment of both subjective parameters of patient satisfaction and objective improvements in function. Another strength of this study is the longitudinal prospective design, which makes it possible to evaluate the evolution of pre- and postoperative clinical phenotypes [98]. The longitudinal design also allows an extensive follow-up assessment, including early postoperative, short-term postoperative, and long-term postoperative measurements. To our knowledge, no other studies have included early postoperative measurements of pain-related cognitions and emotions in the week following surgery. Most studies focus on preoperative prognostic value of candidate prognostic factors; however, postoperative values might be interesting in prognosis as well. For example, short-term postoperative self-efficacy seems to be a better prognostic factor than preoperative self-efficacy in patients with THA [99]. Finally, we aim to unravel the prognostic role of biopsychosocial factors that are not yet investigated in THA research, including perceived injustice and traumatic experiences. The prognostic factors that will be identified are potential predictors of treatment effect and can improve the accuracy of prognostic models for outcome prediction after THA [100]. In follow-up of the current trial, future randomized controlled trials should further elaborate the causal relationships between identified prognostic factors and treatment outcomes in order to identify predictors of treatment effect. In a future RCT, phenotyping at baseline could be performed in an enrichment design to selectively enroll participants with a specific clinical phenotype. Participants with this clinical phenotype could then be randomized into two groups, receiving either specific treatment targeting the phenotypic prognostic factors or standard care as a control intervention. Consequently, the effect of the intervention on the phenotypic prognostic factor and on the outcome after THA should be compared between the intervention and the control group to determine whether the phenotypic prognostic factor is also a predictor of treatment effect. This might provide information to develop individually-targeted treatment pathways for persons with hip OA, which can further improve phenotype-specific treatments. The combination of precision medicine pathways and careful selection of appropriate candidates for THA might optimize outcomes in pain and disability both before and after THA [1].

In addition to the strengths and innovative aspects of this study, there are also some practical issues and potential limitations to consider. In a recent systematic review [101], we investigated contextual prognostic factors for outcomes in the International Classification of Functioning, Disability and Health activity and participation domain after THA in individuals with hip OA. In this review, the main issues in prognostic factor research in individuals after THA for hip OA were discussed. Currently, most studies on prognostic factors for outcomes after THA have a high risk of bias, with mainly problems regarding study attrition and confounding. Therefore, an important practical consideration for this study will be to limit drop-out and accommodate study attrition of participants. The timepoints for follow-up measurements will therefore be scheduled together with the postoperative monitoring appointments with the surgeon to reduce the burden on participants. Furthermore, confounders will be clearly defined and measured using valid and reliable tools, and will be appropriately accounted for in the statistical analysis. One of the limitations of this study will be that generalizability will be limited to individuals with hip OA eligible for THA, and individuals undergoing direct anterior approach THA, since there is a significant preselection of individuals with hip OA undergoing direct anterior approach THA. Furthermore, no external validation is included in this study protocol. When a certain subgroup classification or prognostic factors will be identified, replication of the findings will be necessary in another sample.

